Finally, we postulate that, in order to be valid, the three measured behavioural markers of apathy should: (1) distinguish patient-caregiver couples from healthy couples; (2) be able to predict the psychological health status of patient-caregiver dyads that is perceived by the caregiver (including the caregiver’s rating of the patient’s level of apathy) on a monthly and daily scale. This validation would provide a solid basis for the development of a tool for the remote follow-up of both individuals with dementia and their caregiver. Besides, we assume that it will be possible to disentangle different apathy profiles by data-driven clustering from the extracted scores on the behavioural markers of apathy. In particular, we should be able to identify distinct apathy profiles depending on the patient’s specific condition (i.e., AD or bvFTD).

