### 2.2. Population and Design of the Study

The ECOCAPTURE@HOME study is based on the recruitment of both patient-caregiver and control couples. Each dyad included in the study will be monitored through a multi-sensor wearable bracelet and questionnaires (on a smartphone application) for a period of 28 consecutive days. We plan to recruit a total of 60 couples between 40 and 85 years old divided into three groups: (1) Twenty patient-caregiver dyads with patients diagnosed with the behavioural variant of Fronto-Temporal Dementia (bvFTD), (2) Twenty patient-caregiver dyads with patients diagnosed with Alzheimer Disease (AD) and (3) Twenty healthy control dyads. Groups will be matched for age and socio-demographic characteristics.

The experimental design, summarised in Figure 2, is built upon the measurement model of the behavioural markers of apathy, presumed to predict the psychological status of the patient-caregiver dyad. Thus, we measure two types of variables on both a daily and a monthly scale:In all the dyads, the three theoretical behavioural markers of apathy: daytime activity level, quality of sleep, and emotional arousal, will be assessed using a pool of metrics extracted from the dyad’s raw passive and active behavioural data according to a hierarchical framework with three levels (raw data < metrics < markers considered as latent concepts);In patient-caregiver dyads only, the caregiver’s perception of the dyad’s psychological state is assessed by the following variables through questionnaires: (1) the patient’s level of apathy, as perceived by the caregiver; (2) the caregiver’s perceived burden; (3) the caregiver’s perceived quality of life.

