#### 2.8.2. Analysis Plan for Primary Objective

First, we will extract the metrics from both passive and active behavioural data on a monthly and a daily basis for all dyads. Using these metrics, we will explore a measurement model for the three assumed behavioural markers of apathy on the two time-scales (with monthly scale metrics for the monthly scale model and daily scale metrics for the daily scale model).

We will use Exploratory Factor Analysis (EFA) and Confirmatory Factor Analysis (CFA) in order to identify the system of metrics organised between the three markers, which is the most adapted to measure them. Statistical criteria for the validation of the measurement model tested in CFA (i.e., Root Mean Square Error of Approximation < 0.08, Standardized Root Mean Square Residual < 0.08, Comparative Fit Index > 0.9, Tucker-Lewis Index > 0.9) will guarantee its good adjustment to the data. The internal consistency of the measures of the three behavioural markers will be assessed using Cronbach’s alpha (>0.70). The reliability of the measures (on a daily scale) will also be evaluated through the correlations between the behavioural marker scores obtained on four time-steps (once a week) during the 28-day follow-up (high correlation indicating high reliability).

We will compare the measurement models and mean scores on the three behavioural markers of apathy between groups of patient-caregiver dyads and control dyads (on two time-scales). We will demonstrate that the patient-caregiver dyad’s scores on the three assumed markers of apathy can predict the dyad’s psychological state (as perceived by the spouse caregiver) using linear regression models on the monthly and daily scales. In a perspective of precision medicine, we will also investigate the disentangling of different profiles of apathy, using clustering analyses from the calculated behavioural markers of apathy.

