## 3. Expected Results and Discussion

### 3.1. Expected Results

We expect to identify a fitted measurement model for daytime activity, quality of sleep and emotional arousal from the collected passive and active data in all dyads. This will be the starting point to obtain scores for these three behavioural markers of apathy in each dyad (four scores on a daily scale and one score on a monthly scale). Scores of daytime activity, quality of sleep and emotional arousal are expected to be highly correlated and to distinguish patient-caregiver couples from healthy control couples. Besides, these scores should all contribute to predict the caregiver’s perception regarding the patient’s apathy and regarding his/her own burden and quality of life. Finally, we expect to identify different apathy profiles based on the extracted scores of daytime activity, quality of sleep, and emotional arousal. In particular, as emotional apathy has been shown to be greater in bvFTD than in AD [17,18], we should observe a profile characterized by very low emotional arousal in bvFTD.

Regarding the secondary objectives, we expect to be able to identify which behavioural marker (daytime activity, quality of sleep, or emotional arousal) best predicts the different self-reported measures of apathy. In particular, we can expect the initiation (or auto-activation) component of apathy (DAS-Initiation) to be specifically related to daytime activity whereas the emotional apathy subtype (DAS-Emotional) should be more linked with emotional arousal. Moreover, we globally expect to provide evidence of a close and reciprocal relationship between the patient’s behaviour/status and caregiver’s behaviour/status (e.g., strong causal impact between patient’s and caregiver’s physiological status assessed by sensor data). The caregiver’s state should have an impact on the subsequent measure of daytime activity, quality of sleep, and emotional arousal and reciprocally.

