**Assessment of the Severity of Dementia and of Clinical Symptoms of Interest (1 h)**	
30 min	For patients, Clinical Dementia Rating (CDR): severity of dementia symptoms in three domains (cognition, autonomy, behaviour).
30 min	For all the participants, − Apathy Scale (AS, self-reported version) − Dimensional Apathy Scale (DAS) − Epworth Sleepiness Scale (ESS).

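### The stated validity tests could credit disease type or severity as apathy, because no primary analysis looks at the marker–apathy link within bvFTD and within AD

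*Protocol article*

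**What the plan says.** Section 2.1.1 of the protocol article sets two conditions that the markers must meet to count as valid. They must "distinguish patient-caregiver couples from healthy couples", and they must "be able to predict the psychological health status of patient-caregiver dyads that is perceived by the caregiver", which includes the caregiver's rating of the patient's apathy.

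Section 2.8.2 turns these into analyses. For the first it compares measurement models and "mean scores on the three behavioural markers of apathy between groups of patient-caregiver dyads and control dyads". For the second it sets out to show that the scores "can predict the dyad’s psychological state (as perceived by the spouse caregiver) using linear regression models on the monthly and daily scales". No term for diagnosis or dementia severity is named, and no analysis by diagnosis is described apart from a clustering of marker scores.

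Three other places matter:

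- Section 2.3.1 gives the reasons for enrolling two diseases: to test transnosological validity, and because they are thought to differ in form and severity of apathy, which should widen the spread of the markers. It describes apathy as almost always present in bvFTD and less frequent in AD.
- Section 3.1 predicts that "we should observe a profile characterized by very low emotional arousal in bvFTD".
- Table 1 shows that severity is measured at visit 1, by MMSE and by CDR: "For patients, Clinical Dementia Rating (CDR): severity of dementia symptoms in three domains". Section 2.8 uses neither.

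**The concern.** The article's own premises make diagnosis a candidate common cause. It is expected to shift the predictor (arousal lower in bvFTD) and the outcome (apathy more often present in bvFTD). When two groups differ on both variables, a regression across them shows a slope even if the variables are unrelated inside each group. Dementia severity can act in the same way. The groups are matched on age and socio-demographic characteristics only (section 2.2), and the entry limit on MMSE removes only the most impaired patients.

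The first condition cannot repair this. Anything that dementia changes will separate patients from healthy couples, whether or not it tracks apathy. The actigraphy studies cited in section 1.2 in support of the markers mostly relate activity or sleep to apathy among patients, which is the more informative contrast.

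At stake is the conclusion itself. Section 3.3 looks ahead to a tool for diagnosing and following apathy in individual patients. A marker that mainly indexes which dementia the patient has, or how advanced it is, would not serve that use.

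**Working it through.** **The plan's own figure.** Section 2.8.1 states 591 degrees of freedom and 94.2% power. With 36 metrics there are 36 × 37 / 2 = 666 variances and covariances. The model has 36 loadings + 36 residual variances + 3 factor covariances = 75 parameters, and 666 − 75 = 591. With non-centrality (N − 1) × df × RMSEA², N = 60, RMSEA 0.05 against 0.08 and alpha 0.05 (the article does not print these last three values), power is 94.2%. Both figures reproduce. They concern model fit and do not bear on what the factors measure.

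**Inputs for the check.** From section 2.2: 20 bvFTD, 20 AD and 20 control dyads. From section 2.5: psychological state is measured in patient dyads only, so the regression has at most 40 dyads. Assumed, because the article gives no values: the gap d between diseases, in within-disease SDs and equal on marker and apathy score; no marker–apathy link within either disease; one score per dyad, as on the monthly scale; two-sided alpha 0.05.

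**Second condition, diagnosis as common cause.** With equal groups, the between-group part of each variance is d²/4, so the expected pooled correlation is r = (d²/4) / (1 + d²/4). At d = 1.0 this is 0.25 / 1.25 = 0.20. At d = 1.5 it is 0.5625 / 1.5625 = 0.36. Simulated regressions of the apathy score on one marker give:

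| Gap (SD) | Pooled r | Significant, no diagnosis term | Significant, diagnosis included |
|---|---|---|---|
| 0.5 | 0.06 | 7% | about 5% |
| 0.8 | 0.14 | 14% | about 5% |
| 1.0 | 0.20 | 24% | about 5% |
| 1.2 | 0.26 | 40% | about 5% |
| 1.5 | 0.36 | 67% | about 5% |

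If all three markers carry the gap and are tested jointly, the unadjusted rates at 0.5, 0.8, 1.0 and 1.2 SD are 7, 17, 30 and 50%.

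**Second condition, severity as common cause.** If severity correlates ρ with both marker and apathy score and there is no other link, the expected correlation is ρ². For an assumed ρ of 0.3, 0.5 and 0.7 (r = 0.09, 0.25 and 0.49), a single marker is significant in 9, 35 and 91% of studies unadjusted, and in about 5% with severity in the model.

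**First condition.** For 40 against 20 dyads, the non-centrality is d / √(1/40 + 1/20) = d / 0.274. At d = 1 this is 3.65, and the t test with 58 df is significant in 94.8% of studies when dementia alone causes the difference.

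**Cost of the diagnosis term.** With one marker and 40 dyads, the smallest significant correlation is t / √(t² + df). Without diagnosis it is 2.024 / √(4.10 + 38) = 0.31. With diagnosis it is 2.026 / √(4.11 + 37) = 0.32. Within one disease (n = 20, 18 df) it is 2.101 / √(4.41 + 18) = 0.44.

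**The case against.** - **The article does not say that diagnosis is left out.** It speaks only of linear regression, and covariates may be listed in a document not shown. This stands as a limit: a reader might infer a decision to pool without adjustment, and the text does not support that. Two things do not rest on the silence. The first condition contrasts dementia with health whatever the covariates, and the transnosological aim has no analysis in section 2.8.2.
- **Both conditions are required.** Passing the patient–control contrast validates nothing alone, so 94.8% is not a false-validation rate. This stands.
- **The zero-link case is pessimistic.** Section 1.2 cites links of apathy with activity and sleep among AD patients, and section 3.1 predicts a bvFTD-specific profile for emotional arousal only. Section 1.1 reports emotional apathy as greater in bvFTD but executive apathy as greater in AD, so a large one-way gap on a single apathy score is not established. This stands for size. It leaves arousal, for which section 1.2 cites no such evidence, as the most exposed marker.
- **There are partial safeguards.** These are the MMSE and MADRS limits, the clustering, and the secondary regressions on self-reported apathy with subscale-specific predictions. They help, but none isolates the within-disease link. A plain disease difference could also appear in the clusters and be read as an apathy profile.
- **Adjustment may remove signal.** Apathy is a diagnostic criterion for bvFTD, and one of its proposed mechanisms is cognitive. Diagnosis and MMSE may therefore carry true apathy variance. This stands, and it is why adjusted results belong beside the unadjusted ones and do not replace them.

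**Conclusion.** The concern holds as a risk in the stated validity tests. The patient–control contrast cannot tell apathy from dementia. The regression, as described, cannot tell a link within patients of one disease from a difference between diseases that the article itself expects.

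The size depends on assumed gaps. The false-positive rate for a single marker is close to nominal at 0.5 SD (about 7%), about a quarter at 1.0 SD and about two thirds at 1.5 SD. It is about 5% throughout once diagnosis is in the model. These rates presume no within-disease link and equal gaps on both variables. If only one of the two variables differs between diseases, this bias does not arise.

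A reader might go further and conclude that markers of dementia would be validated as markers of apathy. The documents do not support that: both conditions must be met, the second includes rated apathy among patients, and cited evidence favours a real link for two of the three markers. The supported statement is that disease type or severity could be credited as apathy, and that the planned primary analyses would not show it.

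**What to change.** In section 2.8.2:

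1. Report the regression of caregiver-rated Apathy Scale score on the markers twice, unadjusted and with diagnosis as a covariate.
2. Give the slope within each diagnosis, or a marker-by-diagnosis term, with confidence intervals, and name this as the test of transnosological validity.
3. Base the statement that a marker measures apathy on the within-diagnosis association.
4. Add MMSE and CDR in sensitivity analyses only. Both may overlap with apathy, CDR through its behaviour domain.
5. Report the patient–control contrast as supportive evidence that the markers separate dementia from health.

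A split into more and less apathetic patients is not needed. It would mostly dichotomise the regression already planned.

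The cost is wording and one or two degrees of freedom out of about 40, with no new data. Some true between-disease variance in apathy leaves the adjusted estimate. Slopes from 20 dyads each will be imprecise, so a non-significant slope in one disease should not be read as absence of a link.

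### The hypothesis that apathy profiles differ between bvFTD and AD is addressed only by clustering the marker scores, and no direct bvFTD v AD comparison is named

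*Protocol article*

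**What the plan says.** Section 2.1.1, under the primary objectives and hypotheses, states the expectation and the tool: "we assume that it will be possible to disentangle different apathy profiles by data-driven clustering from the extracted scores". It then ties the profiles to disease: "we should be able to identify distinct apathy profiles depending on" whether the patient has AD or bvFTD. Section 3.1 gives the expected shape: "we should observe a profile characterized by very low emotional arousal in bvFTD".

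Section 2.8.2 gives the analysis: "we will also investigate the disentangling of different profiles of apathy, using clustering analyses from the calculated behavioural markers of apathy". No algorithm or rule for the number of clusters is given there. An article may leave that to a fuller plan, and it is not criticised here.

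Two other statements bear on the point. Section 3.1 says: "Scores of daytime activity, quality of sleep and emotional arousal are expected to be highly correlated". And the comparison of mean scores described in 2.8.2 sets patient-caregiver dyads against control dyads. No section names a comparison of bvFTD with AD on the markers, although diagnosis defines recruitment (section 2.2: 20 dyads per disease) and is known for every patient.

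**The concern.** The hypothesis concerns the shape of the profile: which marker is low relative to the others, by disease. The planned input to the clustering is the scores themselves. When three scores share much of their variance, most of the spread lies along one high-to-low direction. Methods such as k-means and Ward cut where the spread is greatest, so they tend to separate milder from more severe dyads.

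This matters because section 2.3.1 expects bvFTD and AD to differ in severity of apathy as well as in form. A pure severity difference could then produce clusters that line up with diagnosis and be read as disease-specific profiles. A real difference confined to arousal would usually leave the clusters unrelated to diagnosis. The precision-medicine conclusion would rest on an analysis that responds more to severity than to profile.

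**Working it through.** **The plan's own figure.** The only power figure is for the factor model: N = 60, 36 metrics, 3 factors. Degrees of freedom: 36·37/2 − (2·36 + 3·2/2) = 666 − 75 = 591, as stated. Taking close and mediocre fit as RMSEA 0.05 and 0.08, with alpha 0.05 and noncentrality (N−1)·df·RMSEA², power is 0.942. This matches the stated 94.2%. It says nothing about clustering, for which no power is given.

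**Inputs.** 20 bvFTD and 20 AD dyads (section 2.2, before dropout). Three standardised normal scores with common correlation r. The article says only that correlation is high, so r = 0.3 to 0.8 is assumed. Effect sizes are also assumed: 0.8 SD on arousal alone (a profile difference), or 0.8 SD on all three markers (severity only).

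**Step 1: why clusters follow severity.** The common direction carries (1 + 2r)/3 of the variance: 53% at r = 0.3, 80% at 0.7 and 87% at 0.8. Along it, in SD units:
- arousal-only shift d: d/√(3(1+2r)). At d = 0.8 and r = 0.7: 0.8/√7.2 = 0.30.
- severity shift d on all markers: d·√3/√(1+2r) = 0.8·1.732/1.549 = 0.89.

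The severity shift is three times as large in the direction along which the clusters are cut, whatever r is.

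**Step 2: simulation.** Tracking diagnosis means Fisher's exact p < 0.05 for cluster by diagnosis, with two-cluster k-means. The contrast is arousal minus the mean of the other two markers.

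| Truth (r = 0.3–0.8) | k-means tracks diagnosis | Contrast significant |
|---|---|---|
| Arousal only, 0.8 SD | about 6–8% (5–9% in other runs) | 66–99% |
| Severity only, 0.8 SD on all markers | 43–67% | 2–5% |

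Ward clustering gives 7–11% in the first row. With no group difference at all, k-means tracks diagnosis in 2–4% of runs. In one homogeneous population with r of 0.7 or more, the two k-means clusters differ at p < 0.05 on all three markers in 100% of runs and correlate about 0.81 with overall level.

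**Step 3: the contrast in closed form.** Its variance is 1 + (1+r)/2 − 2r = 1.5(1−r). Power is for a two-sided t-test, 38 df, noncentrality (effect/SD)·√10.

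| r | SD | Power, arousal falls 0.8, others 0 | Power, arousal falls 0.8, others 0.4 (contrast 0.4) |
|---|---|---|---|
| 0.3 | 1.025 | 0.672 | 0.225 |
| 0.5 | 0.866 | 0.812 | 0.296 |
| 0.7 | 0.671 | 0.957 | 0.452 |
| 0.8 | 0.548 | 0.994 | 0.614 |

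The first power column agrees with the simulated 66–99%. The second shows the loss when the other markers also fall. A simple t-test on arousal at 0.8 SD has 66–71% power in simulation, whatever r is.

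**Step 4: methods that can return one cluster.** In a homogeneous population the gap statistic reports more than one cluster in 0–2% of runs, and a covariance-modelling mixture with BIC in 3–5%. With a true arousal-only shift of 0.8 SD, that mixture still finds more than one cluster in only 1–7%. Such methods guard against false profiles but do not test the hypothesis.

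**The case against.** **Certainty of false profiles.** A reader might infer that profiles will appear with certainty when none exist. The document does not support this. It fixes no algorithm. The forced split belongs to methods that cannot return one cluster, where it occurs even at r = 0, and to mixtures that ignore correlation. The methods in step 4 rarely give false profiles, and the choice may sit in a plan that is not shown.

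**Contradiction in section 3.1.** A reader might also infer that highly correlated scores and distinct profiles exclude each other. They do not: r = 0.7 leaves 1 − 0.49 = 51% of one score's variance unexplained by another. The sentence on correlation also covers all dyads, controls included. A within-group r of 0.3 with a 2 SD patient-control gap (40 v 20 dyads) gives a between-group part of (2/3)(1/3)·4 = 0.889 and a pooled r of (0.3 + 0.889)/(1 + 0.889) = 0.63. This is why r is taken down to 0.3. The result in the first row of step 2 persists there.

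**A true difference is bound to be missed.** This holds only for an arousal-only shift. The article says that arousal is very low in bvFTD, not that the other markers equal those in AD. At r = 0.7, with arousal down 1.5 SD and the other two down 0.8 SD, k-means tracks diagnosis in about 74% of runs. That association comes largely from severity, though, so it does not show that the shape was recovered.

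**Other checks in the plan.** Section 2.8.3 allows a comparison with clusters from self-reported apathy, but it is optional and does not test diagnosis. The group comparison in 2.8.2 could be read as covering all three groups. Even so, separate marker means are not a test of shape. Finally, clustering is worded as something to investigate, and the sample size rests on the measurement model. That limits the weight of the point without supplying the missing comparison.

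**Conclusion.** The point holds in a limited form. A diagnosis-specific profile hypothesis is stated among the primary hypotheses, the only analysis named for it is clustering of the scores, and no bvFTD v AD comparison is named. Under the assumed correlations and effects, k-means clusters follow diagnosis in under 10% of studies when the profile truly differs by 0.8 SD on arousal alone, against roughly 43–67% when only severity differs by the same amount. Agreement between clusters and diagnosis is therefore weak evidence for disease-specific profiles, and lack of agreement is weak evidence against them.

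The figures depend on normal scores, equal correlations, 20 dyads per disease without dropout and the assumed effect sizes. The measurement model and its sample size are not affected.

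**What to change.** In section 2.8.2:
- Add a prespecified bvFTD v AD comparison of the three standardised marker scores (diagnosis by marker interaction), with one named contrast: emotional arousal relative to the mean of the other two markers.
- Report it next to the simple bvFTD–AD difference in arousal. The simple difference keeps its power when all markers fall, while the contrast separates shape from severity.
- Keep clustering of the scores as exploratory, with a method that can return a single cluster, and do not read clusters as disease-specific profiles unless the contrast supports it.
- Clustering on each dyad's deviations from its own mean may be added as a sensitivity analysis. It should not replace clustering of the scores: at r = 0.7 and 0.8 it tracks diagnosis in 56% and 68% of runs for an arousal-only shift of 0.8 SD, but in only about 5–33% (raw scores 66–82%) when severity also differs.

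The cost is a few lines of text and a small extra analysis on data already being collected. The downside is that the study may have to report no distinct profiles.
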